#### Statistical methods

Descriptive statistics will be used to evaluate differences in the baseline characteristics of participating patients in the two arms of the trial. Study hypotheses will be tested using an intention-to-treat analysis, whereby all consenting patients who were randomized during the accrual period will be included in the analysis. Analysis of the primary outcome, the proportion in each group that are in control and out of control based on doses of fast-acting beta2-agonists, will be compared using a chi-square test. Changes on the Mini-Asthma Quality of Life Questionnaire (AQLQ) will be compared by independent sample t -tests, and differences between mean change scores will be expressed with 95% confidence intervals (CIs). To deal with missing data we will conduct a sensitivity analysis using multiple imputation [146,147] to explore the effects of missing data on the results. Changes in other secondary outcomes, including COPD HRQL, will be evaluated using t-tests for continuous variables and chi-square for categorical variables [141], such as individual items on the TAM that asked about perceived benefit of features of the system and intention to use the system. While our sample size will limit our ability to conduct extensive multivariate analyses, we will assess which characteristics are associated with changes in the primary outcome using multivariate regression analyses with selecting variables in each model and adjusting for potential effect modifiers, (e.g. self-efficacy, adherence, age, sex).

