**Methods:**

The trial is a parallel multi-centered 2-arm pilot randomized controlled trial. Participants are randomly assigned to one of two conditions: a) MAP and usual care; or b) usual care alone. Individuals will be included if they are between 18 and 70, have a confirmed asthma diagnosis, and their asthma is classified as not well controlled by their physician. Asthma control will be evaluated by calculating the amount of fast acting beta agonists recorded as dispensed in the provincial drug database, and asthma quality of life using the Mini Asthma Related Quality of Life Questionnaire. Power calculations indicated a needed total sample size of 80 subjects. Data are collected at baseline, 3, 6, and 9 months post randomization. Recruitment started in March 2010 and the inclusion of patients in the trial in June 2010.

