### Participants

Participants are recruited from pulmonary clinics in two tertiary care hospitals in Montreal, Canada.

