### Sample Size

The primary outcome for this study is change in asthma control. We hypothesized that use of MAP would be associated with a 10% reduction in the proportion of patients classified as being in poor control. Based on MOXXI-II results, we have estimated that 19% of asthma patients will either be seen in the ED for respiratory-related problems, or use greater than 500 doses of fast-acting beta2-agonists in a 6-month period. Thus the intervention would need to reduce the proportion of asthmatics in poor control to 9% to be considered to be sufficiently effective for policy and practice adoption.

Thus, to detect a 10% difference in proportions, [140] with 80% power using a cutoff for statistical significance of 0.05, the sample size needed is 67 participants in total. To account for attrition and loss to follow-up, we will recruit an additional 13 subjects for a total of 80 participants, and 40 participants per arm [141].

This sample size will also allow us to detect a minimal important difference of .5 on the AQLQ [113,142], using the Mini-AQLQ a difference as large as 0.97 (SD .61) was found to be clinically meaningful and significant [114,143-145].

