### Study Procedure

#### Randomization

Treatment allocation is done by random permutation within blocks with block sizes of 4 and 6. Randomization is stratified by center. The randomization is done independently of centres, coordinator, and clinical staff. The randomization is performed with a randomization algorithm developed as part of the McGill University clinical and health informatics research tool kit. The relevant information is only accessible to an employee of McGill University Health Center who is not involved in the trial. After the inclusion of a participant in the trial and the baseline assessment, the study coordinator receives information concerning the allocation of patients to the intervention or control arm by sequentially generated logs through the study coordinator online system. Therefore, the fidelity of allocation is guaranteed.

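### Mini-AQLQ is compared by a t-test on change scores; an ANCOVA on baseline score and centre would be more precise at almost no cost

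*Protocol article*

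**What the plan says.** The Mini-AQLQ is listed under Primary Outcomes, next to overuse of fast-acting beta2-agonists (FABA). The Statistical methods section fixes how each is compared between arms.

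- Mini-AQLQ: "Changes on the Mini-Asthma Quality of Life Questionnaire (AQLQ) will be compared by independent sample t -tests". The effect is reported as the between-arm contrast in average change, with a 95% interval.
- FABA overuse (yes/no): the proportions, "based on doses of fast-acting beta2-agonists, will be compared using a chi-square test".

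No covariate or stratum is named for either comparison. The Abstract says "Data are collected at baseline, 3, 6, and 9 months post randomization", so a baseline Mini-AQLQ score will be in hand. The Participants section places recruitment in "pulmonary clinics in two tertiary care hospitals in Montreal, Canada", and the Randomization section adds "Randomization is stratified by center".

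The only adjusted model in the article looks for characteristics associated with change in the primary outcome, "adjusting for potential effect modifiers, (e.g. self-efficacy, adherence, age, sex". Neither the baseline value of the outcome nor centre is among its examples, and it is not presented as the treatment comparison.

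**The concern.** A change score takes the whole baseline value off the follow-up value, as if the regression slope of follow-up on baseline were 1. With similar variances at the two times that slope is r, which is below 1. Two things follow. The change score carries variance that a fitted slope would remove. And when the arms differ at baseline by chance, part of that difference passes into the estimate through regression to the mean. Both matter more in a trial of 67 to 80 patients than in a large one.

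Centre is a matter of coherence: the design balances on it and the named comparisons do not use it.

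**Working it through.** **Inputs from the article (Sample Size section).** 67 evaluable patients (taken as 33.5 per arm), 80 recruited (40 per arm), 80% power, significance level 0.05 (assumed two-sided), and a Mini-AQLQ difference of 0.5. The only SD is 0.61. It is attached to a cited difference of 0.97 and is not stated to be the SD of change.

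**Inputs assumed.** r from 0.3 to 0.7, because the article gives none, and an alternative SD of change of 1.0.

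**1. The plan's own Mini-AQLQ statement.** Patients per arm = 2 × (1.960 + 0.842)² × (0.61/0.5)² = 23.4, so 24. With 33.5 per arm, the t-test on change has power of about 0.91. The claim that 0.5 is detectable therefore holds if 0.61 is the SD of change. By the normal approximation, 67 patients keep 80% power only up to an SD of about 0.73.

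**2. Variance of the two analyses.** Let s0 and s1 be the SDs at baseline and follow-up.

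- Change score: s0² + s1² − 2·r·s0·s1
- ANCOVA: s1²(1 − r²)
- Difference: (s0 − r·s1)², which is never negative

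With s0 = s1 = 1 these are 2(1 − r) and 1 − r², so the ratio of ANCOVA to change score is (1 + r)/2.

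| r (assumed) | Variance ratio | 67 patients act like | Power, SD of change 0.61 | Power, SD of change 1.0 |
|---|---|---|---|---|
| t-test on change | 1 | 67 | 0.91 | 0.52 |
| 0.3 | 0.65 | 67/0.65 = 103 | 0.98 | 0.71 |
| 0.5 | 0.75 | 67/0.75 = 89 | 0.97 | 0.64 |
| 0.7 | 0.85 | 67/0.85 = 79 | 0.95 | 0.59 |

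Power is from the noncentral t distribution for a difference of 0.5, with residual SD = SD of change × √((1 + r)/2). Two degrees of freedom are given up for baseline and centre, which is negligible here. At r = 0.9 the ratio is 0.95 and little is gained.

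**3. Chance imbalance at baseline.** The standard error of the baseline difference between arms is √(2/33.5) = 0.24 SD. With equal variances, a fraction (1 − r) of any observed imbalance enters the change-score estimate with reversed sign. At r = 0.5, an imbalance of one standard error moves it by 0.5 × 0.24 = 0.12 SD.

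**4. Centre.** The crude chi-square for FABA was compared by simulation with a centre-stratified Cochran-Mantel-Haenszel test: 40,000 runs, two centres of 34, 1:1 within centre, with the odds ratio implied by 19% against 9%.

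| Control rates by centre (assumed) | Power, crude | Power, stratified | Type I error, crude |
|---|---|---|---|
| 19% / 19% | 0.232 | 0.231 | 0.054 |
| 13% / 25% | 0.218 | 0.220 | 0.050 |
| 9% / 29% | 0.205 | 0.213 | 0.045 |

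Stratifying gains less than one percentage point.

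**5. Chi-square or exact test for FABA.** The pooled rate is (19% + 9%)/2 = 14%. The expected number out of control per arm is 33.5 × 0.14 = 4.7, or 40 × 0.14 = 5.6. Full enumeration, with power at 19% against 9% and type I error at a common 14%, gives:

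| Patients per arm | Test | Power | Type I error |
|---|---|---|---|
| 40 and 40 | uncorrected chi-square | 26% | 5.4% |
| 40 and 40 | Fisher exact | 17% | 2.4% |
| 34 intervention, 33 control | uncorrected chi-square | 23% | 5.2% |
| 34 intervention, 33 control | Fisher exact | 18% | 2.9% |

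**The case against.** The strongest reply is that nothing planned here is wrong. The change-score t-test is a valid comparison, it already uses baseline, and over repeated randomisation it is unbiased. If 0.61 is the SD of change, power for Mini-AQLQ is already about 0.91 and ANCOVA adds only 4 to 7 points. The trial is also a pilot. All of this stands. It limits the point to an improvement in precision, but it gives no reason to keep the less precise analysis as the main one when the baseline score is collected anyway. If the SD is nearer 1.0, the gain is 7 to 19 points.

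A reader might infer more than the article supports:

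- *That the Mini-AQLQ analysis ignores baseline or is biased.* It subtracts baseline. Only the estimate given an observed chance imbalance is shifted.
- *That omitting centre costs material precision.* In the simulated FABA cases, with two centres and allocation balanced within each, it does not.
- *That analysing the amount of FABA dispensed, adjusted for baseline, would bring a large and known power gain.* Any such figure needs a dose distribution and a baseline correlation, and the article gives neither. Much of an apparent gain would come from replacing the yes/no endpoint, which the Primary Outcomes section ties to a guideline-derived limit, and not from adjustment.
- *That expected counts near 5 call for an exact test.* The planned chi-square stays close to 5% at both sample sizes, while Fisher's test is conservative and loses power.

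**Conclusion.** The point holds as a recommended improvement to the Mini-AQLQ comparison. ANCOVA is at least as precise as the change-score test for any r and any pair of variances, apart from a negligible loss of degrees of freedom. With equal variances and an assumed r of 0.3 to 0.7, the change-score test gives up 35% to 15% of its variance unnecessarily. The power figures depend on an SD of change that the article does not clearly state, so they are given for both 0.61 and 1.0.

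Including centre makes the analysis follow the design and should not be presented as a material gain. No fault is found with the validity of either planned test.

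A reader might also hope that better analysis would make up for the small sample. It would not. Detecting 19% against 9% at 80% power needs about 188 patients per arm (two-sided), and the planned FABA comparison has power of roughly 22% to 26% with 67 to 80 in total. That is a separate and much larger problem in the Sample Size section.

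**What to change.** - **Mini-AQLQ.** Make the main comparison an ANCOVA of the follow-up score on arm, baseline score and centre, and report the adjusted difference with its 95% confidence interval. Keep the independent-samples t-test on change as a sensitivity analysis.
- **FABA overuse.** Keep the uncorrected chi-square, or use a centre-stratified version of it. Do not switch to an exact test.
- **Optional.** Add a supportive analysis of the amount of FABA dispensed, adjusted for dispensing before randomisation if the claims extract covers that period. The article defines the outcome only over the last six months of follow-up, so this may need a wider extract. Attach no power figure to it.

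The Mini-AQLQ change costs a few words in the analysis section. It needs no new data, visits or patients.

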#### Asthma Quality of Life

The Mini-Asthma Quality of Life Questionnaire (Mini-AQLQ) was developed to measure the four functional impairments that are most important for adults (symptoms, emotions, exposure to environmental stimuli and activity limitation) [112,113]. It has 15-items measured on a 7-point Likert scale. The Mini AQLQ is widely used in asthma clinical trials because it has good internal consistency (interclass correlation coefficient = 0.83), and a strong cross-sectional correlation with the 32-item AQLQ of 0.9), and moderate level correlation of 0.69 (both cross-sectional and longitudinal correlation) with the Asthma Control Questionnaire [112,114], and it is sensitive to change (reliability index = 0.97) [112].

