#### Health care Utilization

Asthma-related ED visits or hospitalizations will be abstracted from provincial database (RAMQ) using validated algorithms [134] which lists information on the date, type, provider, and location of service delivery (e.g. inpatient, emergency, clinic) for all medical services remunerated on a fee-for-service basis (approximately 86% of all services) [135].

Resource Utilization: "Information on the time spent by the nurse case manager (type of call, who is making the call, duration and reason) will be recorded, and will allow us to address health service research issues and knowledge translation to other practitioners and health care organizations. All health-care resources used during the 6-month follow-up will be considered. Intervention costs will include resources used to develop the web-based tool, train patients and nurses to use the system, administer the intervention (time spent for research data collection will not be included). Real time spent with each patient will be carefully documented by each study case manager. Case manager salary costs will be estimated based on the average pay scale of the Federation of Nurses of Quebec. Physician fees will be based on those set by the Provincial Health Insurance Board [136]. "Healthcare utilisation": Information from the provincial health insurance program administrator, RAMQ, will be obtained on asthma-related ER visits or hospitalizations. Total cost per ED visit will be based on data from earlier studies conducted in the province of Quebec [137,138]. ED visit will be a separate resource item from hospitalization. Hospitalization costs will be based on a Quebec index called the Niveau d'Intensité Relatif des Ressources Utilisées (NIRRU)" [139].

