#### Study Timeline

Recruitment started in March 2010 and the inclusion of patients in the trial in June 2010. Follow-up evaluations are conducted at 3 months, 6 months, and 9 months after randomization.

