#### Informed Consent

Prior to study participation patients receive written and oral information about the study process and required time commitment. Potential benefits (mainly to society) and risks are explained in detail. All individuals who wish to be a participant must sign the MUHC approved consent form. In case of study discontinuation the participant will be asked whether they agree to allow all information collected up to the time of withdrawal to be used.

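### The main Mini-AQLQ comparison is in effect complete-case, although the plan calls it intention-to-treat and keeps multiple imputation for a sensitivity analysis

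*Protocol article*

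**What the plan says.** Four statements in the protocol article bear on this point.

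- **Analysis set.** Statistical methods defines intention-to-treat as meaning that "all consenting patients who were randomized during the accrual period will be included in the analysis".
- **Test.** The same section says: "Changes on the Mini-Asthma Quality of Life Questionnaire (AQLQ) will be compared by independent sample t -tests". The difference in mean change is to be given with a 95% CI. No visit is named.
- **Missing data.** The only provision is: "To deal with missing data we will conduct a sensitivity analysis using multiple imputation".
- **Visits.** Study Timeline says: "Follow-up evaluations are conducted at 3 months, 6 months, and 9 months after randomization".

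Sample Size adds 13 participants to 67 to cover attrition, for a total of 80 (40 per arm). Informed Consent says that those who discontinue will be "asked whether they agree to allow all information collected up to the time of withdrawal to be used". Data security says that participants mail completed questionnaires to the study office.

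**The concern.** An independent-samples t-test on change can use only participants who have both scores. Nothing in the main analysis fills the gap for the others, so the main comparison cannot include all randomised patients as promised. The reported estimate and CI would describe completers under an intention-to-treat label, and no rule says which result governs if the imputation analysis disagrees.

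The stakes are a possible bias and some loss of information. The Mini-AQLQ depends on participants returning questionnaires. Only the MAP arm is asked to log in weekly and is re-contacted when it does not, so different dropout in the two arms is plausible, though the document does not predict it. If people with poor early change leave more often from one arm, the completer contrast shifts. Scores from 3 or 6 months, where collected, would help to correct this.

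**Working it through.** **1. The statements side by side.** Set promised: all randomised, 80. Set that a change-score t-test can use: participants with a baseline score and a score at the analysed visit. Expected loss: 80 − 67 = 13, and 13/80 = 16.25%; conversely 67/(1 − 0.1625) = 80, so the allowance is consistent with itself. (Whether 67 is itself the right number is a separate question and is not used here.) On the plan's own allowance, about 13 people would be missing from the main comparison.

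**2. Assumptions for the size of the bias.** The document gives 0.5 as the minimal important difference and 0.61 as its only SD. The rest is assumed:

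- score SD 0.61 or 1.0;
- the same correlation ρ between any two visits, 0.5 or 0.7;
- month 9 as the analysed visit;
- dropout after month 3, with log-odds of leaving changing by 1 per SD of month-3 change where it is related to outcome;
- loss of 16.25% in each arm, or 25% v 7.5%. With 40 per arm the latter is 10 + 3 = 13, the plan's own total.

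**3. Simulation, 100,000 per arm, no true effect.** Bias in the completer difference (MAP minus control), in points:

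| Loss MAP / control | SD 0.61, ρ 0.5 | SD 0.61, ρ 0.7 | SD 1.0, ρ 0.5 | SD 1.0, ρ 0.7 |
|---|---|---|---|---|
| 16.25% / 16.25%, unrelated to outcome | 0.000 | −0.002 | −0.004 | 0.004 |
| 16.25% / 16.25%, poorer responders leave in both arms | 0.000 | 0.000 | −0.008 | −0.001 |
| 25% / 7.5%, poorer responders leave in both arms | 0.043 | 0.035 | 0.070 | 0.056 |
| 25% / 7.5%, control loss unrelated to outcome | 0.061 | 0.050 | 0.114 | 0.081 |
| 16.25% / 16.25%, opposite mechanisms | 0.088 | 0.067 | 0.142 | 0.106 |

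The two 25% / 7.5% rows give 0.035 to 0.114, or about 0.04 to 0.11. When the month-3 score was used to fill in missing values, the difference was within 0.007 of zero in every row. That is simulation noise: the full data were off by up to 0.008.

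**4. Check by formula.** Bias = r × SDΔ × (m_MAP − m_control).

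- SDΔ = SD × √(2(1 − ρ)), which is SD at ρ = 0.5 and 0.775 × SD at ρ = 0.7.
- r = (1 − ρ)/(2(1 − ρ)) = 0.5 is the correlation between two changes that share a baseline.
- m is the mean standardised month-3 change among those who stay. By numerical integration it is 0.213 at 25% loss and 0.069 at 7.5%, and 0 if loss is unrelated to outcome.
- Low end: 0.5 × (0.775 × 0.61) × (0.213 − 0.069) = 0.034. High end: 0.5 × 1.0 × 0.213 = 0.107. Both agree with the simulation.

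If 0.61 to 1.0 is read instead as the SD of change, and 0.5 to 0.7 as the correlation between changes, the same formula gives 0.5 × 0.61 × 0.144 = 0.044 up to 0.7 × 1.0 × 0.213 = 0.149. The order of magnitude is unchanged.

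**5. Scale.** 0.04/0.5 = 8% and 0.11/0.5 = 22% of the minimal important difference. With 30 v 37 analysed and ρ = 0.5, the standard error of the difference is SD × √(1/30 + 1/37), which is 0.150 (SD 0.61) or 0.246 (SD 1.0). The bias is then 0.043/0.150 = 0.29 to 0.114/0.246 = 0.46 of a standard error.

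**The case against.** The strongest reply is that the plan already contains an imputation analysis, so only the order of two analyses is in dispute, and that details of imputation belong in an analysis plan that is not shown. The second half stands: the imputation model is no finding. The first half does not settle the matter, because the article itself fixes which analysis is main and attaches the intention-to-treat label to it.

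Four stronger readings are tempting, and the document does not support them.

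- **That everyone leaving after month 3 or month 6 is excluded.** This presumes a month-9 endpoint. Month 9 is the last evaluation, but Statistical methods names no visit, and Health care Utilization says "All health-care resources used during the 6-month follow-up will be considered". If month 6 were analysed, those leaving after it would stay in.
- **That interim scores are discarded.** They are unused in the main comparison, but the planned imputation could use them, and Informed Consent provides for use of data collected before withdrawal if the participant agrees. The Abstract and Study Timeline also imply, but do not state, that the Mini-AQLQ is given at every visit.
- **That the result will be biased in favour of MAP.** Nothing in the document says who will leave. Stopping the portal is not leaving the study, and controls could leave too.
- **That this is the trial's headline result.** The Mini-AQLQ stands under the Primary Outcomes heading, but Sample Size and Statistical methods name asthma control as the primary outcome, and the latter goes on to speak of other secondary outcomes. Asthma control comes from dispensing records, so it does not depend on questionnaire return.

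**Conclusion.** The point holds in a limited form. The stated analysis set and the stated main Mini-AQLQ analysis do not fit together: as written, the main estimate and CI rest on participants with a score at an unnamed visit, in a trial that allows for 13 of 80 to be lost.

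Bias is possible, not established. It requires dropout that is related to outcome and that differs between arms in rate or mechanism; a difference in rate alone is not enough. Under the assumed 25% v 7.5% loss it is about 0.04 to 0.11 points, roughly 0.3 to 0.5 of a standard error. Under opposite mechanisms it is about 0.07 to 0.14. It is about zero when dropout is unrelated to outcome or alike in both arms. The SD of 1.0, the correlations, the arm-specific loss and the strength of the dropout mechanism are all assumptions. The near-zero bias after using month-3 scores follows from simulating dropout that depends only on those scores. The change is worth making because it is cheap and brings the analysis into line with its label.

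**What to change.** 1. Name the visit at which Mini-AQLQ change is analysed, and state at which visits the questionnaire is given.
2. Make the main analysis one that uses all collected Mini-AQLQ scores of every randomised participant, within the consent terms for those who withdraw. Either a repeated-measures mixed model with arm by visit, or multiple imputation including baseline and interim scores, would do. In either case report the between-arm difference at the named visit with its 95% CI. If the mixed model is chosen, enter baseline as one of the repeated outcomes, so that participants with only a baseline score are not lost.
3. Keep the completer t-test as the sensitivity analysis.

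The cost is a change of wording, with no added visits if the questionnaire is given at the scheduled evaluations. The downside is a slightly more complex model that assumes missingness depends on observed scores. If dropout also depends on unobserved scores, some bias remains.

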#### Engaging and training patients to manage their asthma

Self-management is the individual's ability to manage the symptoms, treatment, physical, and psychosocial consequences and lifestyle changes inherent to living with a chronic health condition [46]. Beyond providing education and supportive counselling, self-management programs also teach specific skills with proven effectiveness [10,16,47,48]. The impact of self-management on health outcomes is thought to occur primarily through changes in health behaviours by providing patients with the confidence to engage in tasks and to acquire core knowledge and skills aimed at helping them better manage their health [16,49].

Optimal long-term management requires ongoing monitoring of asthma control by patients, coupled with an individualized written asthma action plan. This allows patients to quickly identify and address suboptimal disease control by adjusting medications or by contacting their physician [50-52].

Many individuals with asthma lack the necessary knowledge to effectively manage their asthma such as how to avoid common triggers and the role of medications in preventing and addressing worsening symptoms [16,53]. Often, patients do not recognize early signs of exacerbations [54,55]. It is estimated that less than 40% of patients regularly monitor their symptoms [56] and even fewer initiate their prescribed action plan at the first signs of an exacerbation [57,58]. As a result, even when an action plan is available, only a minority of patients titrate their therapy as directed [57,58]. In turn, the exacerbation may escalate to the point of requiring urgent medical attention with an increased risk of morbidity and mortality [59].

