#### Medication Adherence

Adherence to controller asthma medications will be evaluated by comparing medications prescribed to medications dispensed based on the prescription claims in the RAMQ system. This will be calculated using validated methods we developed to adjust quantities dispensed for prescriptions filled before and immediately before the end of the time window for assessment [111].

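### The supplementary regression adjusts for effect modifiers, two of them also trial outcomes; adjustment cannot show modification, and selecting variables on about 9 to 11 events would be unstable

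*Protocol article*

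**What the plan says.** After the main comparisons, the Statistical methods section of the protocol article adds a regression. Its stated aim: "we will assess which characteristics are associated with changes in the primary outcome". Its method: "multivariate regression analyses with selecting variables in each model", and "adjusting for potential effect modifiers, (e.g. self-efficacy, adherence, age, sex". The sentence opens with a caveat: "While our sample size will limit our ability to conduct extensive multivariate analyses".

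Two of the four named variables appear elsewhere in the article in another role:

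- **Self-efficacy.** The adapted self-efficacy scale is listed under Secondary Outcomes. The background describes self-management support as building self-efficacy, and says of the mechanism: "The impact of self-management on health outcomes is thought to occur primarily through changes in health behaviours by providing patients with the confidence" to act.
- **Adherence.** The Medication Adherence section, also under Secondary Outcomes, says: "Adherence to controller asthma medications will be evaluated by comparing medications prescribed to medications dispensed". Table 1 lists adherence to preventative medication among the behaviours that MAP is designed to support.

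The treatment comparison on the primary outcome is separate and unadjusted. The proportions in and out of control, "based on doses of fast-acting beta2-agonists, will be compared using a chi-square test", are analysed by intention to treat, and Mini-AQLQ change is compared by t-test.

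**The concern.** Three things in that one sentence do not fit together.

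1. **Adjustment is not a test of modification.** A variable entered only as a covariate leaves the model with a single arm effect, the same at every level of that variable. Whether MAP works better in some patients is then not examined.
2. **Two covariates lie on the intended causal path.** Measured after randomisation, self-efficacy and adherence are partly consequences of MAP. Holding them fixed would remove the part of the effect that runs through them, and could add confounding by any common cause of the mediator and asthma control.
3. **The outcome is sparse.** The primary outcome is overuse of rescue medication, yes or no. With few events, choosing among four or more variables gives coefficients and selected sets that would change from sample to sample.

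At stake is what this pilot passes on to later studies about which patients improve. The main treatment comparison is not at stake.

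**Working it through.** The plan gives no figure for this regression to reproduce. The checks use its Sample Size section.

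**Inputs.** Poor-control proportions of 19% (control) and 9% (MAP); 67 participants needed and 80 recruited, 40 per arm; four covariates named as examples. I take 67 and 80 as given. Whether 67 follows from the stated power inputs is a separate question and does not affect the event counts.

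**Expected events** = n per arm × (0.19 + 0.09).

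- N = 67: 33.5 × 0.28 = 9.4
- N = 80: 40 × 0.28 = 11.2
- No effect, 19% in both arms: 67 × 0.19 = 12.7; 80 × 0.19 = 15.2

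**Events per parameter.**

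| Scenario | Events | Four covariates | Arm + four covariates |
|---|---|---|---|
| 19% v 9%, N = 67 | 9.4 | 2.3 | 1.9 |
| 19% v 9%, N = 80 | 11.2 | 2.8 | 2.2 |
| 19% both, N = 67 | 12.7 | 3.2 | 2.5 |
| 19% both, N = 80 | 15.2 | 3.8 | 3.0 |

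The true event rate is uncertain in both directions. The 19% counts emergency visits as well as overuse, whereas the outcome is overuse only, which points to fewer events. Entry requires poor control, which points to more. There is an upper bound: the smaller of events and non-events cannot exceed half the sample, so arm plus four covariates can never have more than 40/5 = 8 per parameter at N = 80, or 33.5/5 = 6.7 at N = 67.

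**Adjustment against interaction.** With logit P = b0 + b1·arm + b2·Z, the arm log-odds ratio is b1 whatever Z is. Only with an added b3·arm·Z does it become b1 + b3·Z, and b3 is the modification. This holds whether Z is measured before or after randomisation.

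**Size of the mediator problem if follow-up values were used** (illustrations with assumed coefficients, not estimates for this trial).

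*Linear case.* Let T be arm, U an unmeasured common cause, M adherence, and U and the errors have unit variance: M = 0.5T + 0.5U + e, and Y = 0.25T + 0.5M + 0.3U + e.

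- Total effect: 0.25 + 0.5 × 0.5 = 0.50.
- Given T and M, the expected U is k(M − 0.5T), with k = 0.5/(0.25 + 1) = 0.4.
- Arm coefficient adjusted for M: 0.25 − 0.3 × 0.4 × 0.5 = 0.19, below even the direct effect of 0.25.

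*Binary case, by simulation.* Arm shifts self-efficacy and adherence by 0.5 SD each, each carries a log-odds of −0.85 per SD, and arm has no direct effect. Event rates are 19.8% and 11.0%.

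- Unadjusted arm log-odds ratio: −0.70. Adjusted for both follow-up mediators: 0.02.
- SD of the adjusted arm coefficient: 1.12 at N = 66 and 0.97 at N = 80, after dropping 2.6% and 2.3% of fits that failed or gave extreme coefficients.
- For comparison, the large-sample standard error without adjustment at N = 66 is √[1/(33 × 0.198 × 0.802) + 1/(33 × 0.110 × 0.890)] = 0.71. With 40 per arm it is 0.64. The data are thin before any covariate enters, and the covariates make it worse.

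Baseline values of the same variables cannot be affected by arm and would not cause this bias.

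**The case against.** The strongest reply is that the bias charge assumes things the article does not say. It does not say that follow-up values enter the model. It lists self-efficacy and adherence beside age and sex as characteristics and modifiers, which suits baseline values, and the Randomization section places a baseline assessment before allocation. Nor does it say that arm is in the model or that an arm coefficient will be read as the MAP effect; the stated aim is association. The selection rule is unstated and could be clinical judgement. Timing and selection rules are details that a condensed article may leave to the full protocol or analysis plan. The sample-size limit is admitted in the same sentence. Mini-AQLQ also sits under the Primary Outcomes heading, and events per parameter would not apply to a model of it.

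Most of this stands. A reader might infer that the trial's treatment effect will be biased, or that stepwise selection is planned; the text supports neither. Three things remain:

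- Calling adjustment the way to handle effect modifiers is wrong as stated, whatever the timing.
- The caveat concedes the sample-size limit, yet the same sentence commits to the models. The Sample Size and Statistical methods sections treat asthma control as the primary outcome, so the sparse binary model is the natural reading.
- The wording allows post-randomisation values of two variables that the article itself treats as outcomes and mechanisms.

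**Conclusion.** The concern holds for a supplementary analysis. Covariate adjustment will not answer the modification question. On the design rates there are about 9 to 11 events, or 13 to 15 with no effect, which is about 2 to 3 per parameter with arm and four covariates. Selecting variables on that basis would be unstable. The counts rest on the 19% and 9% assumptions, but the conclusion does not depend on them closely, since no event rate gives more than 8 per parameter.

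Bias in an arm coefficient is a possibility, not a finding. It needs follow-up values, arm in the model, and that coefficient read as the effect of MAP. The chi-square test of the primary outcome and the Mini-AQLQ t-test do not use this regression and are untouched. The change is worth making because it is cheap and the pilot is meant to inform later studies.

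**What to change.** - Use only values from before randomisation: baseline self-efficacy, adherence over a fixed window before randomisation, age and sex.
- Replace selection within each model with a very small set named in advance.
- Assess modification by one arm-by-baseline-variable interaction at a time, preferably on a continuous outcome such as Mini-AQLQ. On the binary outcome even arm, modifier and interaction leave only 9.4/3 = 3.1 to 11.2/3 = 3.7 events per parameter.
- Label the analysis exploratory.
- Analyse follow-up self-efficacy and adherence only as outcomes, or in an explicitly labelled mediation analysis.

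The cost is analysis wording, plus dispensing records for the pre-randomisation window in both arms if they are not already being obtained. Fewer models are reported, and the interactions will be imprecise. For an evenly split modifier and a continuous outcome, the standard error is 4/√n SD against 2/√n for the arm effect: 0.49 against 0.24 SD at n = 67, and 0.45 against 0.22 SD at n = 80.
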